***Treatment of hyperbilirubinemia***

All infants will receive care for hyperbilirubinemia as determined by the treating physician. This treatment typically consists of phototherapy, intravenous fluids, and monitoring of the infant’s bilirubin levels. Therapy is guided by the child's bilirubin level as plotted on a nomogram49 (see Appendix 5). The level at which phototherapy is discontinued depends on age and risk factors of the child (gestational age, hematological disorder, concomitant sepsis, anoxia at birth, etc) and is determined by the nomogram. Once phototherapy is discontinued, intravenous fluids are weaned off and bilirubin is then monitored off treatment. Infants are usually discharged home once their bilirubin is below the threshold for phototherapy, as determined by the nomogram, and off intravenous fluids.

**4.7 Study Measurements:**

Baseline information about the infant and the infant’s mother will be recorded at the time of study enrollment. Information about the mother will include language spoken (French or English), maternal age, number of children prior to the participating infant, number of previously breastfed children, maternal education level, household income, marital status, maternal smoking history during pregnancy and after delivery, type of health care provider who followed the pregnancy, attendance at pre-natal classes. Information about the infant will include age, birth weight, gestational age at birth, weight on admission, weight on discharge, need for IV therapy during the hospitalization, septic work up done on admission, antibiotic treatment, length of stay, and the need for formula supplementation before admission, as well as during hospital stay (see Appendix 6).

Follow-up measurements will be collected until the infant is six months of age. Mothers will be given a booklet upon discharge from the hospital, where they will be asked to record the information on formula introduction, solid food introduction, timing of return to work, number of daily formula feeds and sessions at the breast at different points in time, number of hospitalizations and reason, number of visits to primary care physicians and reason, discussion with primary care physician regarding breastfeeding, number of visits to breastfeeding support (see Appendix 6).

A second research assistant, blinded to group allocation, will phone the participating mothers 1 week after discharge from the hospital to remind them to fill out their booklet, and to collect information regarding breastfeeding and formula feeding. Other phone calls will be placed again when the infant is 2, 3, 4 and 6 months old, to remind the mothers to fill out their booklets. The research assistant will also collect the same information the women are asked to record in their booklet, as a back up method in case the booklets are lost or not appropriately filled out. The research assistant will also remind the families, at the beginning of the phone call, not to disclose whether they were allocated to the control or to the study group so that the research assistant can remain blinded.

Feedback on the intervention will be obtained via semi-structured phone interviews. Twenty women from the intervention group will be randomly selected. Consent to contact the mothers for the purpose of these interviews will have been obtained on the original consent form signed at enrollment. A first set of phone interviews will occur at the end of the intervention period (after the 3 follow-up sessions with the lactation consultant are completed), and at the end of the study period (after the 6 month follow-up period). The interview tool (see Appendix 7) will elicit information on the participants’ perceptions of the intervention. More specifically, what they found most and least helpful, and what changes they would like to see if a breastfeeding support program were to be implemented at the hospital.

Semi-structured phone interviews will also be conducted with women from the control group to gather information on their experience at CHEO, and to determine whether they believe they received adequate support with breastfeeding (see Appendix 8). Twenty women from the control group will be randomly selected for interviews. Consent to contact the mothers for the purpose of these interviews will have been obtained on the original consent form signed at enrollment. A first set of phone interviews will occur one week after hospital discharge, and at the end of the study period (after the 6 month follow-up period).The semi-structured interviews will be conducted for both groups by the first research assistant, as that person will not be blinded to group allocation as he / she will be the person contacting the lactation consultant for mothers allocated to the intervention group.

At the end of the study period, an International Board Certified Lactation Consultant, independent of the study, will be asked to review 10% of the files kept by the study lactation consultant to ensure that advice provided to women met standard of care, as defined by the International Board of Lactation Consultants.

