# 4. RESEARCH DESIGN

**4.1 Trial Design:** This will be a randomized controlled trial with a qualitative component. Blinding of the participants in each study group will not be feasible, as the intervention group will receive counseling from a lactation consultant and the control group will not. The investigators, data analyst, and research assistant completing study follow-up will be blinded to group assignment.

**4.2 Population:** Mothers of all breastfeeding infants admitted to the inpatient units of the Children’s Hospital of Eastern Ontario (CHEO) with jaundice will be considered for this study. CHEO is a tertiary care centre that provides pediatric care to a population of 1.5 million people.

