**4.8 Outcomes:**

***Primary:*** The primary outcome measured will be exclusive breastfeeding at 3 months, or 3 months corrected if the infant was born prematurely. Exclusive breastfeeding is defined as no other milk intake than maternal milk. Health benefits have been demonstrated after as little as two weeks of exclusive breastfeeding50. However, a larger number of studies have reported positive health outcomes after two to four months of exclusive breastfeeding27, 50-52. Exclusive breastfeeding was chosen as primary outcome as it is a quantifiable measure. Partial breastfeeding is more difficult to define as it may range from very little breastfeeding to almost exclusive breastfeeding, which would have an impact on the magnitude of benefits imparted by breastfeeding. Breastfed babies will be defined as babies who receive no other milk than breast milk, whether directly from the breast or as expressed breast milk.

***Secondary:*** All measurements will be collected at corrected age if infant was born prematurely. 1) Exclusive breastfeeding at six months; 2) Partial breastfeeding at three months; 3) Partial breastfeeding at six months; 4) Number of re-hospitalization for jaundice in the first six months of life; 5) Number of re-hospitalization for non-jaundice related causes in the first six months of life; 6) Number of physician encounters in first 6 months of life; 7) Number of mothers seeking breastfeeding help; 8) Amount and type of breastfeeding support given by child’s primary physician in first six months of life

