**5.4 Feasibility**

In 2006, there were 116 breastfeeding infants admitted with jaundice to the Children’s Hospital of Eastern Ontario who met the eligibility criteria of this study, as determined by the CHEO Health Record Analyst. Given that the average length of stay for these patients was 2.5 days, we estimate that 90% of the families admitted to the hospital will be approached, and that 80% of those will consent to participate in the study, for a total enrolment rate of 72%. Based on these numbers, the period of recruitment will last 18 months to achieve our total sample of 124, for a total study duration of 2 years.

Our 90% approaching rates are based on strong strategies put in place to avoid missing eligible patients. As mentioned above, the average length of stay is 2.5 days for babies admitted with jaundice, with very few babies staying less than 24 hours. The admission log will be checked every morning from Monday to Friday by the research assistant, and eligible families will be approached. On Friday afternoon, the research assistant will leave 2 to 3 opaque envelopes in a secure location on the wards. On Saturday and Sunday mornings, the attending physicians responsible for the inpatient units will determine if any of the babies admitted over the previous 24 hours are eligible for the study Eligible families will then be approached by the attending physician on that day. If the family agrees to participate, the attending physician will open the opaque envelope, and communicate with the lactation consultant if randomized to the intervention group. The family will then meet with the lactation consultant if randomized to the intervention group, since the lactation consultant will be available 7 days a week. The attending physician will then be instructed to leave a voice mail message with the research assistant, so that follow-up can be ensured. On Monday morning, the research assistant will pick up the unopened envelopes from the secure location. One of the investigators (CP, AP) will be available by pager to answer the attending physician’s questions, if any. If we find that less than 90% of families are being approached, other strategies will be put in place, such as 24 hours paging of the investigators and/or research assistant by the admitting clerk.

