**Appendix 1**

**Screening Log**

| **Screening #** | **Medical Record Number** | **Date of Visit**  **(dd/mm/year)** | **Eligible**  **for Study** | **Enrolled**  **in Study** | **If YES,**  **Enrollment**  **study #** | **If No, Why?**  **Circle**  **Reason** | **Signature** |
| --- | --- | --- | --- | --- | --- | --- | --- |
|  |  |  | **Y / N** | **Y / N** |  | 1-2-3 |  |
|  |  |  | **Y / N** | **Y / N** |  | 1-2-3 |  |
|  |  |  | **Y / N** | **Y / N** |  | 1-2-3 |  |
|  |  |  | **Y / N** | **Y / N** |  | 1-2-3 |  |
|  |  |  | **Y / N** | **Y / N** |  | 1-2-3 |  |
|  |  |  | **Y / N** | **Y / N** |  | 1-2-3 |  |
|  |  |  | **Y / N** | **Y / N** |  | 1-2-3 |  |
|  |  |  | **Y / N** | **Y / N** |  | 1-2-3 |  |
|  |  |  | **Y / N** | **Y / N** |  | 1-2-3 |  |
|  |  |  | **Y / N** | **Y / N** |  | 1-2-3 |  |
|  |  |  | **Y / N** | **Y / N** |  | 1-2-3 |  |

Legend : 1- Research Assistant not available

2- Family refused enrollment

3- Other

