**Appendix 4**

**Parent Diary**

**Patient Study Number: _________**

Please use this diary to record the types and amounts of food you have given your baby, the medical attention your baby has required, and the breastfeeding advice and help you have received.

This information should be recorded at the following times:

- one week after discharge from hospital
- when your baby is 2 months old
- when your baby is 4 months old
- when your baby is 6 months old

A research assistant will call you at these times to remind you to complete this diary. She will also ask you the same questions.

**REMEMBER**, please DO NOT disclose to this research assistant which study group you were assigned to (Lactation Consultant or Standard Care).

At the end of the study, please mail this diary back to:

Research Coordinator – Breastfeeding Study

[name]

Children's Hospital of Eastern Ontario

Department of Pediatrics

[name]

Ottawa, Ontario

[name]

If you have questions, please contact:

___________________, Research Coordinator, Breastfeeding Study

[contact] x______

[contact]

**Please complete 1 week post-hospital discharge:** ___________________ (date)

**Please record the types and quantities of food sources your child has been given or is currently receiving (please check and complete all sections that apply):**

□ *Breast Milk*

□ Currently, my child feeds at the breast an average of ____ times per 24 hour period. Each feeding lasts approximately ____ minutes.

□ Currently, my child receives expressed breast milk ____ times per 24 hour period. Each feeding is approximately ____ mL or ____ ounces.

□ My child is exclusively breast fed (receives only breast milk).

□ I completely stopped breastfeeding on _________________ (date)

□ *Formula*

□ I introduced my baby to formula on ________________ (date)

□ Currently, my child receives formula an average of ____ times per 24 hour period. Each feeding is approximately ____ mL or ____ ounces.

□ I stopped all formula on _________________ (date)

□ *Other milk (cow’s milk, soy milk, rice milk, goat’s milk, etc.)*

□ I introduced my baby to other milk on ________________ (date)

□ Currently, my child receives other milk an average of ____ times per 24 hour period. Each feeding is approximately ____ mL or ____ ounces.

□ I stopped all other milk on _________________ (date)

□ *Solids (pabulum, cereals, other prepared foods)*

□ I introduced my baby to solids on ________________ (date)

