**Since discharge from hospital . . .**

**Please record information about any medical assessments your child has had (family doctor or pediatrician, ED, hospital visit or admission):**

Date Provider Reason

________ ______________ ____________________________________________________________

________ ______________ ____________________________________________________________

________ ______________ ____________________________________________________________

**If you have seen your child’s family doctor or pediatrician, please describe any advice or help you have received regarding breastfeeding:**

*Date Description of advice or help*

________ ______________________________________________________________________________

________ ______________________________________________________________________________

________ ______________________________________________________________________________

**If you have sought advice or help regarding breastfeeding from someone else, please describe who you approached (private lactation consultant, public health nurse, public breastfeeding clinic, friend, family member, other) and the advice you received:**

*Source Description of advice or help*

________ ______________________________________________________________________________

________ ______________________________________________________________________________

________ ______________________________________________________________________________

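### Readmissions, their cause and emergency visits rest only on the unblinded mother's report, although the trial holds the medical record number that would allow a check at the study hospital

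*Protocol*

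**What the plan says.** Section 4.8 lists as secondary outcome 4 the "Number of re-hospitalization for jaundice in the first six months of life", as outcome 5 the same count for other causes, and as outcome 6 physician encounters. Section 5.2 compares all three between groups by Poisson regression and counts emergency room visits among the encounters.

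Section 4.7 sets the source. The mother keeps a booklet that covers "number of hospitalizations and reason, number of visits to primary care physicians and reason". A second research assistant, blinded to allocation, phones her one week after discharge and when the infant is 2, 3, 4 and 6 months old. The assistant takes the same information "as a back up method in case the booklets are lost or not appropriately filled out". The diary in Appendix 4 words the item as "Please record information about any medical assessments your child has had (family doctor or pediatrician, ED, hospital visit or admission", with blank lines for date, provider and reason. It comes back once: "At the end of the study, please mail this diary back to" the research coordinator.

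On blinding, section 4.1 says "Blinding of the participants in each study group will not be feasible". On records, the Appendix 1 screening log has a column "Medical Record Number" on the same row as the enrolment study number. Section 5.4 reports 116 breastfeeding infants admitted with jaundice in 2006 "who met the eligibility criteria of this study, as determined by the CHEO Health Record Analyst". Section 8 expects to judge impact on health in the first six months partly by the number and length of hospitalizations.

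**The concern.** An admission or emergency visit is a documented event. Its ascertainment need not depend on whether a mother keeps answering the phone, or on how someone who knows the allocation describes it. As planned, it depends on both.

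The reason she gives is the only information from which an admission can be placed under outcome 4 or outcome 5. An infant readmitted with both weight loss and jaundice could be described either way, and no discharge diagnosis is consulted. The arms also differ in contact: under section 4.6 intervention mothers are offered three follow-up visits at which the baby is weighed and signs such as weight loss or jaundice are acted on, and control mothers are not. This could affect how a reason is described, although the documents do not show that it does.

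At stake are the credibility and completeness of the health-care-utilization comparison, which is a stated secondary objective in section 1.2.

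**Working it through.** **1. Is there any second source?** The places that say how data are obtained, set side by side:

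- Section 4.7 and Appendix 4: the mother's booklet.
- Section 4.7: phone calls to the same mother. The caller is blinded and the informant is not.
- Appendix 6: a hospital data form limited to baseline items and the index admission (weights, cultures, fluids, phototherapy, length of stay).
- Section 4.6: the lactation consultant can send an infant to the emergency department and notify the principal investigator. This exists in the intervention arm only and is not named as an outcome source.

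No section provides for chart review, a diagnosis check or adjudication of readmissions. The data source is fixed in the protocol itself, and an analysis plan could not recover data that were never collected.

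**2. Length of readmission.** Section 8 names it. The booklet list in 4.7 does not include it, the diary gives each contact a single date, and Appendix 6 records length of stay for the index admission only. It has no stated source.

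**3. The plan's own figures.** Section 5.1 gives 58 per group for 50% versus 75% (two-sided 0.05, 80% power). The usual two-proportion formula without continuity correction returns 58, with power 0.802. After allowance for 7.5% loss the protocol recruits 62 per group, 124 in total. It states no rate, power or sample size for readmissions.

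**4. Infants with incomplete counts.** Infants affected = total randomised × proportion lost.

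- Protocol's ceiling, stated for the primary outcome at 3 months: 124 × 0.075 = 9.3, about 9 infants.
- Assumed 10% to 20% loss by 6 months (no figure is given): 124 × 0.10 = 12.4 to 124 × 0.20 = 24.8.

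**5. Readmissions of any cause at risk of being missed.** The rate is an assumption: 0.05 to 0.20 readmissions per infant over six months.

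- Expected in the trial: 124 × 0.05 = 6.2 to 124 × 0.20 = 24.8.
- Falling in infants lost, at 7.5%: 6.2 × 0.075 = 0.5 to 24.8 × 0.075 = 1.9.
- If loss occurs at 3 months and events are spread evenly, half of that is missed: 0.2 to 0.9.

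**6. Jaundice readmissions.** Assume 2% to 5% of infants per arm. Then 62 × 0.02 = 1.2 to 62 × 0.05 = 3.1, so roughly 1 to 3 events per arm. One event missed or placed under the wrong cause is between 1/3 and 1/1 of an arm's count, a change of 33% to 100%.

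**7. Can one event decide significance in that range?** As a simple guide, use the exact conditional test with equal arms, in which the events split as binomial(n, 1/2). The most unequal starting point is 3 versus 1.

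- Remove one from the smaller arm: 3 v 0, p = 2 × (1/2)³ = 0.25.
- Add one to the larger arm: 4 v 1, p = 2 × (5 + 1)/32 = 0.375.

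Neither is near 0.05.

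**The case against.** The case for leaving the plan alone has real substance.

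- **Infants lost do not lose their whole count.** A reader might infer that an infant whose mother stops answering has no readmission count. Section 4.7 does not support that: the calls at 1 week and at 2, 3 and 4 months keep whatever was reported up to the last contact. What is lost is later events and, if it is never mailed, the diary. Enrolled infants are under one month old, and section 2.1 describes jaundice as an immediate post-natal problem, so jaundice readmissions probably fall mostly before attrition. This stands. The gap matters more for outcomes 5 and 6.
- **The mother is not said to make the jaundice split.** A reader might infer that she classifies each admission. She writes a free-text reason. The protocol does not say who assigns the category, and under section 6.1 the blinded second assistant collects and enters the data. This stands too, but whoever classifies has only her words to work from.
- **One event will not swing the test.** A reader might point out that 5 v 0 gives p = 2/32 = 0.063 and 6 v 0 gives p = 2/64 = 0.031, so that a single event could cross 0.05. Those counts lie outside the assumed 1 to 3 per arm, and the planned analysis is Poisson regression rather than this exact test. The documents do not support that reading.
- **No differential error is shown.** A hospital admission is memorable and is asked about at intervals of about two months or less. That is fair: unequal reporting is possible, not demonstrated.
- **The remedy is partial.** The extract covers one hospital. A catchment of 1.5 million does not show that infants return there, and a coded main diagnosis carries some ambiguity of its own. This is true, and it limits the gain without removing it.

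**Conclusion.** The point holds as a cheap improvement to secondary outcomes 4, 5 and part of 6. It is not an error that threatens the trial: the primary outcome, the sample size and the main conclusion are untouched.

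Three facts rest on the documents alone: maternal report is the only source for readmissions, their cause and emergency visits; cause has no diagnosis check; and length of readmission has no stated source. The 9 of 124 infants with incomplete counts rests on applying to six months a 7.5% ceiling that the protocol states for three months, so it may be too low.

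The effect on the between-group comparison cannot be sized, because the protocol gives no readmission rate. Under the rates assumed in the working, fewer than about two readmissions of any cause would be missed at 7.5% loss. A single jaundice event would alter an arm's count noticeably without by itself deciding significance.

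**What to change.** In sections 4.7 and 4.8, state that:

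- at six months, admissions and emergency visits at the study hospital (date, length of stay, main discharge diagnosis) are extracted by medical record number for every randomised infant, including those lost to phone follow-up;
- the extract is made by the already blinded second research assistant or the data management group, and is limited to those fields so that nothing in the wider record reveals the allocation;
- jaundice versus other cause is classified from the discharge diagnosis, blind to group;
- maternal report is kept for other hospitals and for community physician visits, and the source of each event is recorded.

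The cost is one records query for 124 infants, subject to consent that covers record access. The consent form is not among the pages available, so whether it already does cannot be seen; if it does not, a line must be added. Sample size, intervention and primary analysis do not change. The downside is mixed sources: events at this hospital would be ascertained equally in both arms whatever the retention, while contacts elsewhere would still depend on the mother. Recording the source allows the two to be reported separately.
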